### Outcomes

Outcome measures will be collected at baseline (T0), after 6 months (T1), which corresponds to the end of the training programme for the experimental group, and at the 12-month (T2) follow-up by healthcare professionals blinded to patients’ allocation.

*The primary outcome* will be the measurement of the 6 min walking distance (6MWD) performed during the 6 min walking test.^41^ The variations in mobility assessed by 6MWD will be determined at the end of the programme in relation to the baseline. The patients will be instructed to walk back and forth along a 20 m corridor, aiming to cover as much distance as possible. Patients will also have to report the onset of any symptoms during the test, and the correspondent distance will be recorded as pain-free walking distance. When necessary, they will be allowed to stop as needed and restart whenever possible. Patients will also be monitored with a pulse oximeter to check their corresponding saturation. The rate of perceived exertion will be recorded on the 0–10 Borg scale at the end of the test.

*Secondary outcomes* will include the following:

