### Statistical methods

Standard methods for the analysis of RCTs will be employed. All analyses will be conducted using intention-to-treat, where any subject randomised to one arm remains in that arm regardless of whether they received the intervention.

Missing values, although we will make any effort possible to reduce their incidence, will be treated using the multiple imputation procedure. Moreover, a sensitivity analysis will be performed to assess the stability of the study’s conclusions, comparing the intention-to-treat analysis with an analysis that takes into account the level of participation in the intervention arm. A p value <0.05 will be considered statistically significant. Several statistical analysis software packages, including SPSS, MedCalc and Stata, will be used.

A Shapiro-Wilk test will verify the nature and distribution of the data. At baseline, the two groups will be compared in terms of demographics and primary and secondary outcome measures. Although our initial hypothesis suggested the superiority of the exercise group over the control group, to account for the possibility that participants in the control group might achieve better outcomes than those in the intervention arm, we will use two-tailed tests of significance for all analyses. For categorical variables, the χ^2^ test or Fisher’s test will be employed, as appropriate. Overtime between-group differences will be analysed using t-tests for symmetrically distributed data and analogous non-parametric tests, such as the Mann-Whitney test, for skewed data. A two-way repeated measures analysis of variance (factors: treatment, time) will be run to compare differences over time for secondary outcomes. Paired-sample t-tests or Wilcoxon tests will assess the within-group variations. Suppose a significantly different distribution between the two groups in the baseline outcome level is identified. In that case, a secondary analysis will be performed using multivariate modelling, such as analysis of covariance, to adjust for these factors. For the long-term outcomes, Kaplan-Meier curves with log-rank tests and Cox proportional hazard regression models will be performed.

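### Secondary outcomes: the repeated-measures ANOVA is a valid test but gives no baseline-adjusted difference at 6 or 12 months, and adjustment depends on a baseline significance test

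*Protocol article*

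**What the plan says.** The Outcomes section sets three assessments: "Outcome measures will be collected at baseline (T0), after 6 months (T1"), which is the end of training, "and at the 12-month (T2) follow-up".

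The Statistical methods section then names several analyses that can apply to the same secondary outcome:

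- Between groups: "Overtime between-group differences will be analysed using t-tests for symmetrically distributed data", with "analogous non-parametric tests, such as the Mann-Whitney test, for skewed data". The sentence is not limited to the primary outcome.
- Secondary outcomes: "A two-way repeated measures analysis of variance (factors: treatment, time) will be run to compare differences over time for secondary outcomes". The article does not say which visits are levels of time, or which term of the model carries the result.
- Within groups: "Paired-sample t-tests or Wilcoxon tests will assess the within-group variations".
- Baseline adjustment is conditional. The trigger is worded as follows: "Suppose a significantly different distribution between the two groups in the baseline outcome level is identified". Only then does the article add analysis of covariance, and it ranks that analysis as secondary.

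Missing values are to be handled by multiple imputation, and all tests are two-sided at 0.05.

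**The concern.** The ANOVA has no covariate, so the baseline value can enter only as a level of time or not at all. The first is the natural reading, and it treats a value taken before randomisation as a response. Two terms could then be read as the result, and neither answers the clinical questions directly.

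- The interaction asks whether the two profiles over three visits differ in any way. It does not say whether the arms differ at T1, at T2 or at both, and it has no single estimate or interval. T1 closes the training period and T2 falls six months later, so these are separate questions.
- The treatment main effect averages over all three visits, including T0, where randomisation makes the expected difference zero.

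The more efficient method, adjustment for baseline, is kept for outcomes that happen to show a significant baseline difference. With sound randomisation and a 0.05 threshold, that is about 1 outcome in 20, and it is chance that selects them. Several analyses can therefore apply to one outcome with no stated lead. Quality of life, strength, body composition and kidney function are all affected.

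**Working it through.** The article gives no power or precision figure for secondary outcomes, so there is none to reproduce.

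**Inputs.** From the article: three visits, two arms, 1:1 allocation, two-sided 0.05. The n = 48 per arm is borrowed from the walking-distance calculation (before the dropout allowance). My assumptions, not in the article: SD 1 at each visit, equal correlation r of 0.5, 0.7 or 0.8 between visits, an effect of 0.5 SD at T1, and three courses to T2. As (T0, T1, T2) these are: sustained (0, 0.5, 0.5), half kept (0, 0.5, 0.25), lost (0, 0.5, 0).

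**What the main effect estimates.** It is the mean of the three visit differences. For a sustained effect d this is (0 + d + d)/3 = 2d/3, so 0.5 becomes 0.333. For an effect lost by T2 it is d/3, so 0.5 becomes 0.167.

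**Formulas.**

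- Interaction: F on 2 and 188 df, noncentrality (n/2) × S/(1 − r). S is the sum of squares of the three differences about their mean: 0.167 (sustained), 0.125 (half kept), 0.167 (lost). At r = 0.7: 24 × 0.167/0.3 = 13.3 (sustained or lost) and 24 × 0.125/0.3 = 10.0 (half kept).
- Main effect: F on 1 and 94 df, noncentrality (n/2) × mean²/v, with v = (1 + 2r)/3. At r = 0.7, sustained: 24 × 0.111/0.8 = 3.33.
- t-test on change at T1: noncentrality 0.5/[√(2(1 − r)) × √(2/48)]. At r = 0.7: 0.5/(0.775 × 0.204) = 3.16.
- Analysis of covariance at T1: noncentrality 0.5/[√(1 − r²) × √(2/48)]. At r = 0.7: 0.5/(0.714 × 0.204) = 3.43.

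**Power.**

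| Test | r = 0.5 | r = 0.7 | r = 0.8 |
|---|---|---|---|
| Interaction, sustained or lost | 71% | 91% | 98% |
| Interaction, half kept | 58% | 81% | 94% |
| Change t-test at T1 | 68% | 88% | 97% |
| Analysis of covariance at T1 | 80% | 92% | 98% |
| Main effect, sustained | 51% | 44% | 41% |
| Main effect, half kept | 32% | 27% | 26% |
| Main effect, lost | 17% | 15% | 14% |

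**Two results follow.** First, S is the same for a sustained and a lost effect, so the interaction test has identical power in both. Its F value alone cannot tell a benefit that lasts from one that disappears. Second, the variance of the adjusted estimate relative to the change score is (1 − r²)/[2(1 − r)] = (1 + r)/2, that is 0.75, 0.85 and 0.90 at the three correlations. Baseline adjustment therefore saves 25%, 15% and 10% of the variance at no cost.

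**The case against.** The case for leaving the plan alone is substantial. A reader might draw stronger conclusions in four ways that the article does not support.

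- *The ANOVA dilutes the treatment effect.* Shrinkage to 2d/3 or d/3 belongs to the main effect only. The article speaks of comparing differences over time, which points to the interaction, and that is not diluted. With only T0 and T1 in the model, the interaction has the same power as the t-test on change (88% for both at r = 0.7). The low main-effect powers describe a term that the article never singles out.
- *Secondary outcomes get only omnibus tests.* The sentence just before the ANOVA plans t-tests or rank tests between groups and does not confine them to the primary outcome. Read as tests of change, the t-tests give a difference and an interval at each visit.
- *The interaction is badly underpowered.* The half-kept course gives the smallest S for any T2 effect, so it is the least favourable case. With a sustained or lost effect and r = 0.7, the interaction has 91% against 92% for analysis of covariance, and at r = 0.8 the two are level.
- *Multiple imputation and ANOVA are incompatible.* Imputation supplies the complete data that the ANOVA needs, and pooled tests for multi-parameter hypotheses exist. The awkward pooling, mainly for rank tests, is an inconvenience and not a contradiction.

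It is also fair that baseline as a level of time is inferred, and that a full analysis plan, not shown, could name the term, the contrasts and the pooling. What stands is the choice that the article itself makes: an unadjusted ANOVA for secondary outcomes, with adjustment triggered by a baseline test. A baseline-adjusted contrast would be clearer, and at low to moderate correlation more powerful than the t-test on change.

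**Conclusion.** The point holds as a moderate improvement confined to secondary outcomes. The planned ANOVA is a valid test, and the 6-minute walking distance result does not rest on it. Its weakness is that it yields no visit-specific difference with an interval, while the t-test that does so gives up precision that the recorded baseline would supply.

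At T1 the gain from adjusting over the change-score t-test is about 12 percentage points of power at a correlation of 0.5, 4 to 5 at 0.7, and about 1 at 0.8. Against the interaction, the gain runs from none (effect sustained or lost, correlation 0.8) to about 22 points (half kept, correlation 0.5). That comparison is not like for like, because the interaction also uses T2. All these figures rest on the assumed 0.5 SD effect, 48 per arm and equal correlations. The 2d/3 shrinkage needs none of those assumptions, but it matters only if the main effect is read as the result.

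**What to change.** Replace both the two-way ANOVA and the conditional analysis of covariance with one prespecified baseline-adjusted analysis for every continuous secondary outcome. This can be analysis of covariance at each visit, or a linear mixed model on T1 and T2 with treatment, visit, treatment-by-visit, the baseline value and the randomisation strata. Report the adjusted between-group difference with 95% CI at T1 and at T2, and drop the baseline significance test as a trigger.

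If multiple imputation is kept, these estimates and standard errors pool directly by Rubin's rules. For skewed outcomes, a robust or bootstrap standard error keeps the same estimate and avoids switching to a rank test.

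The cost is a change of wording, with no new patients, visits or measurements. It should be made before the statistician sees outcome data by arm.

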### Sample size and recruitment

The feasibility of this study is assessed by analysing the prevalence of patients with CKD-PAD in the hospitals involved in this project. We identified a cohort of over 200 patients potentially meeting the inclusion criteria. In each centre, a network of physicians, including nephrologists, internists and vascular surgeons, will be established to identify potentially eligible patients and facilitate enrolment. Every centre will identify a responsible person for enrolment to assess patients’ eligibility and manage their inclusion in the randomisation list.

We calculated the sample size, hypothesising the superiority of the experimental treatment over the control group. A sample of 96 patients, 48 in each group, is needed to detect a 30 m improvement in 6 min walking distance in favour of the experimental group, assuming an SD of improvement of 30 m, with a type I error of 0.05 and a power of 90%. To account for possible dropouts, the sample size will be increased by 30%, resulting in a total of 124 patients to be enrolled.

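### The primary comparison of 6MWD change leaves out baseline 6MWD as a covariate; ANCOVA is only a secondary analysis, run after a significant baseline test. Naming it as primary is a free improvement.

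*Protocol article*

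**What the plan says.** The Outcomes section makes the primary measure a change from baseline: "The variations in mobility assessed by 6MWD will be determined at the end of the programme in relation to the baseline". The Sample size and recruitment section works on the same scale. It plans 48 evaluable patients per arm for a between-arm difference of 30 m, and its variability assumption also refers to change: "assuming an SD of improvement of 30 m, with a type I error of 0.05 and a power of 90" per cent.

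The Statistical methods section then sets out four steps.

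- Baseline comparison: "At baseline, the two groups will be compared in terms of demographics and primary and secondary outcome measures".
- Between-arm test: "Overtime between-group differences will be analysed using t-tests for symmetrically distributed data and analogous non-parametric tests", with the Mann-Whitney test as the example for skewed data.
- Repeated-measures analysis of variance, which "will be run to compare differences over time for secondary outcomes". It is therefore not the primary analysis, and the t-test or Mann-Whitney test is what remains for 6MWD.
- Baseline adjustment, under a condition: "Suppose a significantly different distribution between the two groups in the baseline outcome level is identified". What follows when the condition is met is stated next, and it ranks below the primary test: "In that case, a secondary analysis will be performed using multivariate modelling, such as analysis of covariance, to adjust for these factors".

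The same section sets the significance threshold at 0.05 and makes all tests two-sided.

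**The concern.** In a properly randomised trial, any baseline difference between arms is due to chance. A significance test of that difference does not show whether adjustment is worthwhile. The value of adjusting depends on how strongly baseline 6MWD predicts 6-month 6MWD, and this is the same whether the baseline p value is 0.04 or 0.60.

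Two things follow. First, a change score subtracts baseline with a slope of 1, whereas ANCOVA estimates the slope, which is normally below 1. The planned estimate therefore carries avoidable noise. Second, when one arm starts lower by chance, regression to the mean favours that arm in a change-score comparison, and an imbalance just short of significance prompts no adjusted analysis. Even when the trigger fires, the adjusted result ranks second, so the primary result is never baseline-adjusted.

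**Working it through.** **Inputs from the document.** Target difference 30 m, SD of change 30 m, two-sided alpha 0.05, power 90%, 48 per arm, 1:1 allocation.

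**Assumptions.** The correlation rho between baseline and 6-month 6MWD is not given, so I use 0.7, 0.8 and 0.9. The SD of 6MWD is taken as equal at the two times. The figures are for the t-test version of the primary analysis.

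**1. The plan's own sample size.** n per arm = 2 × (1.960 + 1.282)² × (SD/difference)².

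- SD 30 m: 2 × 10.507 × 1 = 21.01, so 22 per arm (23 with the exact t distribution). This does not give 48.
- SD 45 m: 2 × 10.507 × 2.25 = 47.28, so 48 per arm.

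The stated 48 per arm thus matches an SD of change of about 45 m. That is a separate matter, but it is why power is shown below at both SDs.

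**2. How often the trigger fires.** By construction, 5% of correctly randomised trials. A simulation (40,000 trials, 48 per arm) gave 4.8% to 5.1%.

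**3. Precision.** With a common SD s, Var(change) is proportional to 2s²(1 − rho) and Var(ANCOVA) to s²(1 − rho²). The ratio is (1 + rho)/2:

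- rho 0.7: 0.85
- rho 0.8: 0.90
- rho 0.9: 0.95

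**4. Power at 48 per arm (noncentral t).**

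| SD of change | Change score | ANCOVA, rho 0.9 | rho 0.8 | rho 0.7 |
|---|---|---|---|---|
| 30 m (stated) | 99.8% | 99.9% | 99.9% | above 99.9% |
| 45 m | 89.8% | 91.3% | 92.6% | 93.9% |

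At 45 m the gain is 91.3 − 89.8 = 1.5 points up to 93.9 − 89.8 = 4.1 points.

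**5. Residual shift from chance imbalance.** Given a baseline imbalance, the change-score estimate is shifted by (1 − rho) times it, in favour of the arm that started lower. For an imbalance of z standard errors, the imbalance is z × s × √(2/48). With s = SD of change/√(2(1 − rho)), the shift is z × SD of change × √((1 − rho)/48).

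| Imbalance | SD of change | rho 0.9 | rho 0.8 | rho 0.7 |
|---|---|---|---|---|
| Median, z = 0.67 | 30 m | 0.9 m | 1.3 m | 1.6 m |
| Just below trigger, z = 1.9 | 30 m | 2.6 m | 3.7 m | 4.5 m |
| Median, z = 0.67 | 45 m | 1.4 m | 2.0 m | 2.4 m |
| Just below trigger, z = 1.9 | 45 m | 3.9 m | 5.5 m | 6.8 m |

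**6. Error rate.** Over all randomisations, the simulated rejection rate of the change-score test with no effect was 4.9% to 5.0% (rho 0.5, 0.8 and 0.9). Given the imbalance, the estimate is normal with the shift in step 5 and variance (1 + rho)/2 of the change-score variance. The conditional two-sided error for rho 0.9 to 0.7 is then:

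- z = 0: 4.4% to 3.4%
- z = 0.67: 4.7% to 4.1%
- z = 1: about 5.0%
- z = 1.9: 6.5% to 9.4%

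**The case against.** The strongest reply is that the planned test is sound. An unadjusted comparison of change is unbiased over randomisation and holds its 5% error rate, so ANCOVA is a gain in efficiency and repairs nothing invalid. This stands, and it sets the weight of the point.

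Three stronger readings are tempting, and the document supports none of them.

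- *The plan ignores baseline 6MWD.* It does not. The outcome is a change from baseline and the sample size uses an SD of improvement, so each patient's baseline is subtracted. It is missing only as a covariate.
- *Imbalance below the trigger goes uncorrected.* A change score corrects it, somewhat too much. What remains is 10% to 30% of the imbalance at rho 0.9 to 0.7.
- *The baseline test selects the primary result and distorts its error rate.* As written, the triggered ANCOVA is added as a secondary analysis and never replaces the primary test.

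The conditional error of 6.5% to 9.4% also belongs to a rare case: about 0.7% of trials have an imbalance between z = 1.9 and z = 1.96. Up to about z = 1, the conditional error is at or below 5%.

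Finally, at the stated SD of 30 m there is almost no power to gain. That is correct, but the reassurance is limited, because 48 per arm does not follow from that SD.

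It cannot be said that the matter is simply left to a fuller analysis plan. The article states the rule itself.

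**Conclusion.** The point holds as a free improvement. The primary analysis is valid but leaves out a covariate that is measured in every patient, and it ties the only adjusted analysis to a test that carries no useful information under randomisation.

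The loss is modest: 5% to 15% of variance for a correlation of 0.9 to 0.7. Against the 30 m target, the residual shift is usually one or two metres and reaches 4.5 m just below the trigger at the stated SD. The effect on power ranges from negligible to about 4 points, depending on whether the SD of change is nearer 30 m or 45 m.

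These sizes rest on an assumed correlation and on equal SDs at the two visits. The structural point, that the primary result is never baseline-adjusted and that about 95% of trials would have no adjusted analysis, does not depend on them.

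**What to change.** In Statistical methods:

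- Name ANCOVA as the primary analysis: 6-month 6MWD regressed on arm and baseline 6MWD in all randomised patients, reported as an adjusted mean difference in metres with a 95% confidence interval, whatever the baseline data show.
- Delete the rule that makes adjustment depend on a significant baseline difference, and describe baseline characteristics by arm without p values.
- Keep the unadjusted comparison of change as a sensitivity analysis.

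The cost is a change of wording and one model degree of freedom. Baseline 6MWD is already collected, so no new data are needed.

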### Allocation

After the recruitment procedure at baseline, the physician responsible for enrolment in the Coordinating Centre will create the allocation sequence on a password-protected computer. An external administrator not involved in the trial will then randomise patients to one of the two groups using a computerised randomisation stratification approach to prevent selection bias. The random assignment will be communicated to investigators on the day of enrolment by accessing it on identification in an online repository. Only one coordinator of each centre will be permitted to access the participants’ allocation. The randomisation scheme (1:1 ratio) will be established using permuted blocks of random sizes. The block sizes will not be disclosed to ensure concealment. Finally, the subjects will be assigned to one of two study groups: the exercise (Ex) group or the control (Co) group.

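### The primary 6MWD comparison is an unadjusted t-test or Mann-Whitney test picked from the data, with ANCOVA only after a significant baseline difference; one pre-specified ANCOVA would be more precise

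*Protocol article*

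**What the plan says.** All references are to the protocol article.

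- **Outcome.** Under Outcomes, the primary outcome "will be the measurement of the 6 min walking distance (6MWD) performed during the 6 min walking test", and "The variations in mobility assessed by 6MWD will be determined at the end of the programme in relation to the baseline". That makes the primary variable a change from baseline to 6 months.
- **Test.** Under Statistical methods: "Overtime between-group differences will be analysed using t-tests for symmetrically distributed data and analogous non-parametric tests, such as the Mann-Whitney test, for skewed data". The only distribution check named is this: "A Shapiro-Wilk test will verify the nature and distribution of the data". Repeated-measures analysis of variance is assigned to the secondary outcomes, so the two-sample test is the one left for the primary outcome.
- **Baseline.** "At baseline, the two groups will be compared in terms of demographics and primary and secondary outcome measures". The rule for adjustment opens with a condition: "Suppose a significantly different distribution between the two groups in the baseline outcome level is identified". Only when that condition is met does the plan call for a model: "In that case, a secondary analysis will be performed using multivariate modelling, such as analysis of covariance, to adjust for these factors".
- **Missing data.** The same section names multiple imputation.

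No section makes a baseline-adjusted model the primary analysis. These are stated rules, so the point does not rest on detail that an article would leave to a fuller plan.

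**The concern.** Baseline 6MWD is measured in everyone and can be expected to predict 6-month 6MWD. The plan uses it in the primary comparison only by subtraction. It is modelled with an estimated slope only when a significance test on the baseline values is positive. In a randomised trial that test asks whether a difference known to be due to chance is due to chance, so its result is no guide to whether adjustment helps. An imbalance below the threshold still moves a change-score estimate. An imbalance above it leaves the unadjusted result as primary in just the trials where it is least reliable.

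The second data-driven step is the choice between t-test and Mann-Whitney. The trial is sized on a difference in mean improvement in metres. A Mann-Whitney test addresses a different quantity and supplies no mean difference and standard error to combine over the imputed data sets. What the primary analysis estimates would therefore be settled only after the data are seen.

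**Working it through.** **Inputs from the article (Sample size and recruitment):** difference 30 m, SD of improvement 30 m, type I error 0.05 (two-sided, from Statistical methods), power 90%, 48 per arm.

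**Assumptions:** the correlation ρ between baseline and 6-month 6MWD is not given, so 0.5 to 0.9 is shown. The SD of 6MWD is taken as equal at the two times.

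**1. The plan's own figure.** n per arm = 2(1.96 + 1.2816)² × 30²/30² = 21.01, so 22 (23 with the t distribution), not 48. An SD of change of 45 m would give 21.01 × (45/30)² = 47.3, so 48. That mismatch is a separate matter. Here it only means that results are shown both at the stated 30 m and at 45 m, the latter an assumed value.

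**2. Precision.** With SD σ at each time, the change score has variance 2σ²(1 − ρ) and the ANCOVA residual has variance σ²(1 − ρ²). The ratio is (1 + ρ)/2, below 1 for every ρ below 1.

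**3. Shift from chance imbalance.** If the arms differ by D at baseline, the change-score estimate is off by −(1 − ρ)D on average: the arm that starts higher is penalised. The baseline SD is σ = SD of change/√(2(1 − ρ)). The largest non-significant D is 1.96 × σ × √(2/48). For ρ = 0.8 and SD 30 m: σ = 30/√0.4 = 47.4 m, D = 1.96 × 47.4 × 0.204 = 19.0 m, shift = 0.2 × 19.0 = 3.8 m.

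| ρ (assumed) | ANCOVA / change-score variance | SD 30 m: largest D → shift | SD 45 m: largest D → shift |
|---|---|---|---|
| 0.5 | 0.75 | 12.0 → 6.0 m | 18.0 → 9.0 m |
| 0.7 | 0.85 | 15.5 → 4.6 m | 23.2 → 7.0 m |
| 0.8 | 0.90 | 19.0 → 3.8 m | 28.5 → 5.7 m |
| 0.9 | 0.95 | 26.8 → 2.7 m | 40.3 → 4.0 m |

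**4. Power at 48 per arm, 30 m difference.**
- SD 30 m: SE = 30 × √(2/48) = 6.12 m; 30/6.12 − 1.96 = 2.94, power 99.8%. ANCOVA at ρ = 0.8 gives 99.9%. The 95% interval half-width falls from 1.96 × 6.12 = 12.0 m to 12.0 × √0.90 = 11.4 m.
- SD 45 m: SE = 9.19 m, power 90.4%. ANCOVA gives 96.5%, 94.3%, 93.1% and 91.8% at ρ = 0.5, 0.7, 0.8 and 0.9.

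**5. Type I error** (simulation of 20,000 null trials per ρ, 48 per arm; ρ = 0.5 / 0.7 / 0.9).
- Baseline test significant: about 5% of trials (0.050 / 0.048 / 0.049).
- Change-score t-test over all trials: 5.2% / 4.9% / 5.0%.
- Imbalance above 1 SE but not significant: change score 7.7% / 6.2% / 5.7%; ANCOVA 4.9% / 4.7% / 5.4%.
- Baseline test significant: change score 18% / 13.8% / 6.5%; ANCOVA 5.3% / 4.4% / 4.4%. About 1,000 trials fall here, so the 18% carries a simulation SE of √(0.18 × 0.82/1000) = 1.2 points.

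**The case against.** The strongest reply is that an unadjusted change-score t-test is a valid analysis. It is unbiased over randomisation, its overall type I error is near 5%, and at ρ of 0.8 to 0.9 ANCOVA saves only 5% to 10% of the variance. The shifts tabulated are also the worst non-significant case. At the median chance imbalance (0.674 SE) and ρ = 0.8 the shift is 0.674 × 9.68 × 0.2 = 1.3 m at SD 30 m, or 2.0 m at SD 45 m. All of this stands and limits the size of the point. It does not defend the two triggers, since the better analysis needs no extra data.

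A reader might infer more than the article supports:

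- *Chance imbalance is left uncorrected.* It is not. The outcome is a change from baseline, so baseline is subtracted for every patient; the fault is a slope fixed at 1.
- *The primary result is chosen between adjusted and unadjusted answers.* The adjusted model is labelled secondary in advance. Only the choice between t-test and Mann-Whitney is data-driven.
- *Substantial power is lost.* Not at the stated SD.
- *The analysis ignores the randomisation strata.* Allocation mentions "using a computerised randomisation stratification approach to prevent selection bias" but names no factors, and an article may leave those covariates to the full plan.
- *The normality check would often misfire.* Under truly normal data the switch rate is about 10% if each arm is tested and either can trigger, and about 5% for one pooled test. The article states neither rule, so no rate can be assigned.

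**Conclusion.** The point holds as one of precision, conditional bias and an estimand left open to the data. It is not one of overall type I error.

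The firm part needs no assumed SD: with equal SDs at the two times, ANCOVA is more precise than the change score for every ρ below 1, and the baseline trigger brings in adjustment in only about 1 trial in 20. The size depends on ρ, which the article does not give. The shift at the significance threshold runs from 2.7 to 6.0 m at the stated SD over ρ of 0.9 to 0.5, or 9% to 20% of the 30 m target. At ρ = 0.8 it is 13% (19% at the assumed 45 m). If the SD of 6MWD differed between the two times, the shift would be (slope − 1) × D with the actual regression slope in place of ρ.

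The objection to the rank-test switch does not depend on any of these figures. It should be corrected, but it does not invalidate the trial.

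**What to change.** Pre-specify one primary analysis for all randomised patients: ANCOVA of 6-month 6MWD on treatment and baseline 6MWD, plus whatever stratification factors the randomisation uses. Report it as an adjusted mean difference in metres with a 95% confidence interval, pooled over the imputations. Delete the baseline significance test as a trigger for adjustment, and delete the distribution-based switch between tests. Keep the Mann-Whitney test as a sensitivity analysis. Baseline tables can stay as description.

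The cost is a change of wording. Baseline 6MWD is already collected, and neither recruitment nor visits are affected. The change should be made before any outcome data are seen by arm.
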